#### 4.3.1.2 Derivation or calculation of variable

Each variable will be evaluated and presented separately and an overall post-operative infection rate will also be calculated.

#### 4.3.2 Post-operative antibiotics use

##### 4.3.2.1 Methods of assessment

The use of post-operative antibiotics will be assessed at each check up after surgery throughout the study period and registered in the MED log in the CRF.

##### 4.3.2.2 Derivation or calculation of variable

Use of post-operative antibiotics will be expressed in percentage per treatment arm, i.e. number of subjects with post-operative antibiotics/total number of subjects. The total number of days and dose registered in the MED log for post-operative antibiotics will also be presented per treatment arm.

#### 4.3.3 Length of hospital stay

##### 4.3.3.1 Methods of assessment

The day of surgery will represent the start of the hospital stay, since the day of admission can, for various reasons, differ between each subject. The day of discharge will represent the last day of stay. The total length of stay will be divided on type of care facility, i.e. intensive care unit or post-operative care unit. Time per type of care facility will be registered in the CRF.

##### 4.3.3.2 Derivation or calculation of variable

The days between surgery and discharge will be calculated and the total time and time per type of care facility will be compared between treatment groups for every clinic.

#### 4.3.4 Post-operative Hb

##### 4.3.4.1 Methods of assessment

Haemoglobin concentration in g/dl will be assessed together with haematocrit (erythrocyte volume fraction) in percentage pre-operatively and after 3 hours, 24 hours, 2 days and 4 days after surgery. Venous or capillary blood samples will be used.

#### 4.3.4.2 Derivation or calculation of variable

Absolute differences between the treatment groups at each time point and in change from baseline (pre-operatively) will be evaluated.

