### **Screening and inclusion**

- After obtaining the subject's written informed consent and verifying that the subject fulfils all inclusion and none of the exclusion criteria the subject will be included in the study and given a Subject Id.
- A reference venous blood sample/s will be taken from each subject before surgery, for analyses of Hb, haematocrit/erythrocyte particle count (Hct/EVF), sodium ( $\text{Na}^+$ ), potassium ( $\text{K}^+$ ), thrombocyte particle count (TPC), C-reactive protein (CRP), leukocyte particle count (LPC), creatinine and Glomerular Filtration Rate (GFR)/Creatinine Clearance ( $\text{C}_{\text{Cr}}$ ). Haemoglobin (Hb) concentration  $> 9.0 \text{ g/dl}$  ( $5.6 \text{ mmol/l}$ ) and normal creatinine/clearance levels will be verified.
- Subject ID will be allocated based on clinic number and procedure (primary or secondary surgery and treatment group given from randomization).
- Demographics will be collected and registered in the Case Report Form (CRF).
- Medical and surgical history as well as medications will be registered in the CRF.

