#### 6.1.4 Multi-centre

This study is a multi-centre study and there is no a priori reason to suspect that there will be any qualitative differences between the centres. However, local treatment routines at different clinics

are considered to potentially affect the outcome of the primary variable why stratification for each clinic will be made. This is considered to ensure equal distribution between test and control group patients why primary statistical analysis will not include centre in the model. The result of the primary variable will however be presented by centre as part in subgroup analyses.

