## 6.2 Description of outcome variables in relation to objectives and hypotheses

The primary variable, transfusion rate, will be measured as the proportion ( $\pi$ ) of patients in each treatment group that is receiving allogeneic blood transfusion of the total number of patients in each treatment group. The hypothesis to be tested is:

$$H_0 = \pi_s = \pi_c$$

versus

$$H_1 = \pi_s \neq \pi_c$$

Where:

$\pi_s$  = Proportion patients treated with Sangvia® that require allogeneic blood transfusion in addition to Sangvia® transfusion.

$\pi_c$  = Proportion patients in the control group that require allogeneic blood transfusion.

The hypothesis will be tested using the Fischer Exact Test. The hypothesis will be rejected if the p-value is  $\leq 0.05$ .

Secondary objectives will be tested using similar hypotheses. The total and variable specific proportion values for infection rate, use of post-operative antibiotics and adverse events will be tested between the groups using the Fischer Exact Test. Continuous variables (e.g. post-op Hb values) will be compared and tested using the Wilcoxon Rank Sum test. Laboratory blood markers will also be evaluated for changes over time within each treatment group and this change will be tested using the Wilcoxon Signed Rank test.

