## 6.5 Determination of sample size

The primary variable and objective is the base for the sample size calculation. The sample size formula used is referred to in Lachin 1981.

$$N = \frac{(Z_{\alpha} + Z_{\beta})^2 4\bar{\pi}(1 - \bar{\pi})}{(\pi_s - \pi_c)^2}$$

Where:

N = total number of patients

$Z_{\alpha} = 1.96$  ( $\alpha = 0.05$ )

$Z_{\beta} = 1.2816$  ( $1 - \beta = 0.90$ )

$$\bar{\pi} = \frac{\pi_s + \pi_c}{2}$$

An estimation normal use of allogeneic blood of 21% is based on reported values in the literature. It is acknowledged that in revision surgery a higher percentage of allogeneic blood transfusions is seen than in primary total hip replacements. Because revision patients requiring serious bone grafting are excluded, the percentage of revision patients is expected to be just slightly higher than for the average primary total hip. A high number of revision, e.g. a maximum of 30%, in the total group of patients is considered to have limited effect of the total transfusion rate but are accounted for in the 21% assumed for the total group. The expected values of transfusion rate in the Sangvia® group is estimated to lie around 7%. Accordingly, imputing the values for the estimated transfusion rates in the test and control group generates a mean transfusion rate value of 14%. The sample size necessary for detection of this expected difference in transfusion rate frequency is calculated to 260 patients (5% significance level, two-sided hypothesis, 90% power). Additional 40 patients will be included in the study to compensate for drop-out. In summary, 300 patients will be included in total and 150 in each treatment group.

The transfusion rate of bank blood is considered to vary dependent on type and complexity of surgery. Greatest normal use and differences between the groups are expected in the subgroup with medium (surgery duration 1-2 hours) to complex (surgery duration more than 2 hours) surgery complexity why power are considered to be adequate for the planned subgroup analyses in these groups.

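### Pre-operative haemoglobin is collected in every patient but enters the Hb comparison only as a change score, never as a covariate, which costs some precision on a secondary objective

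*Protocol*

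**What the plan says.** Comparing post-operative Hb between patients given Sangvia® blood, no blood or allogeneic blood is a secondary efficacy objective (Protocol Section 2.2).

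The baseline is available. Under Screening and inclusion in Section 3.1, "A reference venous blood sample/s will be taken from each subject before surgery", and Hb is among the analytes. Section 4.3.4.1 confirms it: "Haemoglobin concentration in g/dl will be assessed together with haematocrit (erythrocyte volume fraction) in percentage pre-operatively", with repeat measurements at 3 hours, 24 hours, 2 days and 4 days.

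Two contrasts are planned in Section 4.3.4.2: "Absolute differences between the treatment groups at each time point and in change from baseline (pre-operatively) will be evaluated". The test is fixed in Section 6.2: "Continuous variables (e.g. post-op Hb values) will be compared and tested using the Wilcoxon Rank Sum test". Section 6.4 and the synopsis repeat the rank sum test for continuous variables in general.

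No section plans a covariate-adjusted analysis of Hb. Section 6.1.2, on covariates, provides for stratification by surgery type, subgroup analyses and a test of age balance. Section 6.1.4 adds stratification by clinic.

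**The concern.** A two-sample rank sum test takes no covariate. Applied to the raw post-operative values, it leaves the variation explained by pre-operative Hb in the error. Applied to change from baseline, it removes the pre-operative value with a fixed coefficient of 1, which is best only if the regression slope of post-operative on pre-operative Hb happens to be 1. A covariate analysis estimates that slope, so it is at least as precise as either, apart from the negligible cost of estimating one coefficient.

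The plan also gives two answers at each of four times (2 × 4 = 8 Hb comparisons) and does not say which contrast leads. If the arms differ by chance in pre-operative Hb, the two can point in different directions, and the choice between them would then fall after the data are seen. At stake are the precision and clarity of one secondary efficacy result. The choice is made in the protocol itself, and Section 6.1 makes a separate statistical analysis plan optional.

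**Working it through.** **Inputs**

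- Sample size assumptions, Section 6.5: transfusion rates 21% and 7%, "5% significance level, two-sided hypothesis, 90% power", 260 patients plus 40 for drop-out, equal allocation.
- Evaluable patients: 260, or 130 per arm.
- Hb standard deviation, Hb effect and pre/post correlation r: not in the protocol. Assumed: equal standard deviations before and after surgery, and r from 0.4 to 0.7, with 0.3 and 0.8 as outer checks.

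**1. The plan's own figure.** The Section 6.5 formula gives

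N = (1.96 + 1.2816)² × 4 × 0.14 × 0.86 / 0.14² = 258.2,

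against 260 stated. It reproduces. It concerns the transfusion rate only; no sample size or power is claimed for Hb.

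**2. Relative variance of the Hb group contrast.** With common variance σ²:

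- raw post-operative value: σ², relative variance 1
- change from baseline: σ² + σ² − 2rσ² = 2(1 − r)σ², relative variance 2(1 − r)
- baseline as covariate: (1 − r²)σ², relative variance 1 − r²

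For any r strictly between 0 and 1, 1 − r² is below 1. It is also below 2(1 − r), because 1 − r² = (1 − r)(1 + r) and 1 + r < 2.

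**3. Numbers.** The plan runs both contrasts, so the fair benchmark at each r is the better of the two.

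| r | Raw | Change | Adjusted | Better planned / adjusted | Extra patients | Excess SE |
|---|---|---|---|---|---|---|
| 0.4 | 1.00 | 1.20 | 0.84 | 1.00/0.84 = 1.19 | 19% | 9% |
| 0.5 | 1.00 | 1.00 | 0.75 | 1.00/0.75 = 1.33 | 33% | 15% |
| 0.6 | 1.00 | 0.80 | 0.64 | 0.80/0.64 = 1.25 | 25% | 12% |
| 0.7 | 1.00 | 0.60 | 0.51 | 0.60/0.51 = 1.18 | 18% | 8% |

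Excess SE is the square root of the variance ratio, minus 1. With 260 evaluable patients, the adjusted analysis is worth the better planned contrast run on about 309, 346, 325 and 305 patients at these four values. The loss peaks at r = 0.5. At r = 0.3 it is 1/0.91 − 1 = 10%, and at r = 0.8 it is 0.40/0.36 − 1 = 11%.

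**4. Check with the planned tests.** The formulas compare means, whereas the plan uses rank tests. Normal data were therefore simulated with 130 per arm, 3,000 runs per r, and a true difference of 0.347 SD (assumed; it gives an unadjusted comparison of raw means 80% power).

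| r | Rank sum, raw | Rank sum, change | ANCOVA | Rank ANCOVA |
|---|---|---|---|---|
| 0.3 | 77% | 64% | 83% | 81% |
| 0.5 | 77% | 78% | 90% | 87% |
| 0.7 | 78% | 94% | 97% | 96% |

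Both adjusted analyses had more power than both planned tests at each r tried. The like-for-like comparison is rank ANCOVA against the better rank sum test: 81 against 77, 87 against 78, and 96 against 94. The gain therefore does not depend on giving up a non-parametric method.

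**The case against.** The strongest reply is that nothing here is wrong. Both planned contrasts are randomised comparisons, valid and unbiased. The rank sum test is named consistently, Hb is secondary, and the primary test and sample size rest on transfusion rate. An SAP, if written, could name a lead contrast or add a covariate model. Rank methods also have a particular justification: allogeneic blood is triggered by low Hb (transfusion triggers in Section 3.1), so later Hb values are themselves altered by transfusion. All of this stands, and it limits the point to efficiency and clarity. It does not remove it, because the protocol already fixes an unadjusted test for this variable and a rank-based adjustment is available.

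A reader might infer more, in four ways the protocol does not support.

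- *The plan ignores baseline.* It does not. The change score uses the pre-operative value and recovers most of the available gain when r is high.
- *The loss is as large as 96%.* That figure sets adjustment against raw values alone at r = 0.7 (1/0.51 = 1.96), where the planned change score already has variance 0.60 against 0.51. Likewise, 43% sets it against the change score alone at r = 0.4 (1.20/0.84 = 1.43), where the raw contrast is the better one.
- *The arms will be compared through within-arm tests.* Section 6.2 says of laboratory changes over time that "this change will be tested using the Wilcoxon Signed Rank test", but this is in addition to the between-group tests.
- *The same gain applies to creatinine, CRP or leukocyte count.* No calculation here covers those variables.

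**Conclusion.** The point holds as a minor one. Pre-operative Hb is available for every patient, but it is used only as a change score beside a raw comparison, both tested without covariates, and neither is named as the main result. Against the better planned contrast, the loss is about 18% to 33% in equivalent patients, or about 8% to 15% in standard error.

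That size rests on equal standard deviations and an assumed r of 0.4 to 0.7, neither of which can be checked from the protocol. The direction is firmer. With unequal standard deviations the adjusted contrast is still at least as precise as either planned one, and it equals the change score only if the regression slope is 1. The validity of the Hb comparisons, the primary analysis and the total of 300 patients are not in question.

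**What to change.** In Sections 4.3.4.2 and 6.2, name one baseline-adjusted between-group contrast as the main Hb analysis at 3 hours and days 1, 2 and 4. Either form would serve:

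- ANCOVA of post-operative Hb on treatment arm and pre-operative Hb, with the stratification factors surgery type and clinic, reporting the adjusted difference with its 95% confidence interval; or
- rank ANCOVA, if the non-parametric approach is to be kept. It tests on the rank scale, so the Hb differences in g/dl should be shown beside it.

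Surgery type and clinic are included because patients are stratified on them; no gain in precision from them has been calculated. Section 6.1.4 says that the "primary statistical analysis will not include centre in the model", but that concerns the primary variable and need not change. Keep the rank sum tests on raw values and on change from baseline as sensitivity analyses.

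The cost is analysis wording only: no new data, visits or patients. The change should be made before the data are examined by arm.

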### 4.4 Safety measurements and variables

The methods for collecting safety data are described below.

#### 4.4.1 Adverse Events

##### 4.4.1.1 Definitions

The definitions of Adverse Events (AEs), Adverse Device Effects (ADEs) and Serious Adverse Events (SAEs) are given below. It is of the utmost importance that all staff involved in the study are familiar with the content of this section. The principal investigator is responsible for ensuring this.

##### **Adverse Event**

An Adverse Event (AE) is any untoward and unintended medical occurrence in a subject. This definition does not imply that there is a relationship between the AE and the medical device under investigation. An AE which is possibly related, is one that may have been caused by the medical device, or treatment, however there is insufficient information to determine the likelihood of this possibility.

- Possibly related: temporal relationship of the onset of the event, relative to the use/administration of the medical device, is reasonable but the event could have been due to another, equally likely cause.
- Non-related (unlikely): temporal relationship of the onset of the event, relative to the use/administration of the medical device, is not reasonable or another cause can itself explain the occurrence of the event.

Ambiguous cases should be considered as possibly related.

##### **Adverse Device Effect**

An Adverse Device Effect (ADE) is any untoward and unintended response to a medical device. This definition includes any event resulting from insufficiencies or inadequacies in the instructions for use of the medical device or any event that is a result of a user error. This definition also includes treatment- or procedure- related events. ADEs can only occur from the time of medical device use/administration. Here the event is related to the use of the medical device where there is a probable/definite relationship that the event may have been caused by the medical device, or treatment.

- Probably related: temporal relationship of the onset of the event, relative to the use/administration of the medical device, is reasonable and the event is more likely explained by the medical device/treatment than by any other cause.
- Definitely related: temporal relationship of the onset of the event, relative to the use/administration of the medical device, is reasonable and there is no other cause to explain the event.

### **Serious Adverse Event**

A Serious Adverse Event (SAE) is an AE/ADE occurring during any study phase of the medical device, that fulfils one or more of the following criteria:

- Results in death
- Is immediately life-threatening
- Requires in-subject hospitalisation or prolongation of existing hospitalisation
- Results in persistent or significant disability or incapacity
- Is a congenital abnormality or birth defect
- Is an important medical event that may jeopardise the subject or may require medical intervention to prevent one of the outcomes listed above.

If a non-related AE becomes serious, i.e. fulfilling one or more of the above criteria, action should be taken as for any other SAE.

For further guidance on the definition of a SAE and a guide to the interpretation of the causality question, see Appendix B to the Clinical Study Protocol.

#### **4.4.1.2 Recording of Adverse Events and Adverse Device Effects**

At each assessment point and/or visit, scheduled or unscheduled, the subject will be asked an open question; "Have you had any health problems since the previous visit?"

All AEs must be recorded in the CRF's AE log:

- Time of onset, action taken, outcome and whether the AE constitutes a SAE or not must be specified for events regarded as "possibly/probably/definitely" related to the device by the investigator.
- A short description and whether the AE constitutes a SAE or not must be specified for events regarded as non-related to the device by the investigator.

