### 2.2 Secondary objectives

The secondary objectives of the study are....

....to observe and compare clinical efficacy by means of postoperative infection rates, use of postoperative antibiotics, length of hospital stay and health status for patients transfused with Sangvia® blood, no blood and/or allogeneic blood.

....to observe and compare clinical efficacy by means of systemic postoperative haemoglobin levels for patients transfused with Sangvia® blood, no blood or allogeneic blood.

....to collect details in health care utilisation (medications, in-patient service use, blood management) that would allow a calculation and comparison of cost-consequences applying either alternative in the blood management and from the perspective of the payer

....to observe and compare safety by means of adverse events, highlighting renal failures and events potentially related to transfusion, body temperature and other clinical complications for patients transfused with Sangvia® blood, no blood or allogeneic blood.

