## 3.4 Treatments

### 3.4.1 Identity of investigational product and comparators

The investigational product is the CE-marked Sangvia® Blood Salvage System. The system consists of an intra-operative set, a post-operative set and vacuum tubing that enable collection, filtration and transfusion of intra-operative and post-operative blood.

[figure not shown]

The recommended user instructions for the Sangvia® Blood Salvage System should be followed for set-up, blood collection and reinfusion.

In summary, the collection canister is connected to a suction source with the recommended suction pressure of 100 mmHg (maximum 150 mmHg is allowed) and a suction tip is connected to the inlet tubing of the system. The collection unit is placed lower or at the same height as the operation table and an anticoagulant drip is connected to the system (ACD-A, sodium citrate or CPD) with the recommended ratio of 1:7 (approximately 20 drips per minute). The blood is filtered from larger debris, cement and bone particles by a macro filter of 200µm when collected in the chamber. The upper compartment of the collection unit has a maximum volume of 700 ml and the lower compartment has a maximum volume of 500 ml. When blood is being emptied to the transfusion bag the opening between the upper and the lower compartments should be closed. The blood is filtered from small particles by a micro filter before reinfusion. The reinfusion is initiated when 500 ml blood have been collected or at the end of surgery. Blood transfusion should be completed within 6 hours of the start of collection. Post-operative collection and transfusion will follow after surgery. The post-operative set is set-up and used according to the recommended user instructions. As for the intra-operative collection phase blood transfusion must be completed within 6 hours from start of collection during the post-operative phase. The reinfusion of the post-operatively collected blood may start either when the blood has passed 500 ml in the lower chamber or at the end of the 6 hour collection period. Not more than 2500 ml intra- and/or postoperatively collected blood in total should be transfused to the patients.

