### 3.6 Blinding and procedures for unblinding the study

#### 3.6.1 Methods for ensuring blinding

It is not possible to double blind this study due to the fact that it will be obvious for the study site team to which group the patient has been allocated. I.e. patients in the test group will have their blood collected with the Sangvia® device and in the control group no autologous blood salvage will be performed. The decision of blood bank transfusion will however be assessed in a blinded fashion with an independent assessors unaware of the patient treatment allocation. I.e. each decision of bank blood transfusion will be taken based on transfusion triggers by an assessor unaware of the treatment group whenever possible and the reason/s for the transfusion will be registered. For cases when the decision of bank blood transfusion are taken by a responsible investigator aware of the treatment allocation, e.g. in an emergency situation during surgery, the registered reasons for transfusion will be reviewed by an independent assessor/committee who are unaware of the treatment allocation. Inconsistency in transfusion decision between the independent assessor/committee and the responsible investigator will be reflected in the per protocol analysis where patients with suspected biased transfusion decisions will be excluded. Laboratory sample analyses will be done by assessors unaware of the patient treatment allocation.

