#### 4.3.1.1 Methods of assessment

##### Clinical symptoms of infections:

Clinical symptoms of infections according to the classical signs of inflammation, i.e. swelling, redness, pain, heat and loss of function, and as deemed by the investigator will be regarded as an adverse event and registered in the AE log. Clinical symptoms of infection will be assessed at each check up after end of surgery throughout the study period.

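### Onset, action taken and outcome are mandatory only for device-related adverse events, so non-serious events in controls get a shorter record than ambiguous events in the test arm

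*Protocol*

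**What the plan says.** Section 4.4.1.2 sends every AE in either arm to the AE log, then sets the required content by the investigator's causality call. For events considered possibly, probably or definitely related to the device the rule begins "Time of onset, action taken, outcome and whether the AE constitutes a SAE or not must be specified for events regarded as". For the others, "A short description and whether the AE constitutes a SAE or not must be specified for events regarded as non-related to the device".

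Section 3.4.1 identifies the device: "The investigational product is the CE-marked Sangvia® Blood Salvage System". Section 3.6.1 says who does not get it: "in the control group no autologous blood salvage will be performed". The causality categories in section 4.4.1.1 turn on timing relative to use of the device. For adverse device effects the text adds "ADEs can only occur from the time of medical device use/administration", and for doubtful causality it says "Ambiguous cases should be considered as possibly related".

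One secondary objective in section 2.2 is "to observe and compare safety by means of adverse events, highlighting renal failures and events potentially related to transfusion", across patients given Sangvia blood, no blood or allogeneic blood. Under section 4.3.1.1, clinical symptoms of infection "will be regarded as an adverse event and registered in the AE log".

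**The concern.** The fuller record depends on relatedness to a device that only one arm receives. The same non-serious event can therefore be dated and followed to its outcome in a test patient, yet appear as a short description with a SAE flag in a control patient. The call that decides this is made by a site team that knows the allocation. The trial's blinding measures cover bank-blood decisions and laboratory analyses, not AE causality.

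At stake is the objective of comparing events potentially related to transfusion. Whether an event may be related to a transfusion depends largely on when it began relative to that transfusion. Allogeneic blood is the comparator treatment, but the recording rule asks only about the device.

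**Working it through.** No figure is stated and no power or error rate is involved. The check is a reading of the sections together, plus a small calculation of visit spacing.

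1. **Which record applies to whom.** Relatedness in section 4.4.1.1 is judged against use of the device. The device is Sangvia (3.4.1), which controls do not receive (3.6.1). A control patient's AE, including a reaction to bank blood, is therefore non-related to the device and falls under the short record.

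2. **The test arm.** A clearly unrelated event gets the same short record. A doubtful one must be called possibly related and gets the full record. Take a non-serious febrile episode in a patient who received both Sangvia blood and bank blood: if causality is unclear, it is recorded in full. The same episode in a control patient given only bank blood is not required to be.

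3. **Other sources of the missing fields.** Section 4.4.1.1 treats a non-related event that becomes serious as any other SAE, and section 4.4.1.3 has the sponsor and investigator assemble the information for SAEs in either arm. The SAE report fields are not listed, so full recovery is likely but not certain. No other section requires onset, action taken and outcome for non-serious, non-related events. The gap is therefore in non-serious events.

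4. **What the visits recover.** Patients are asked at each assessment about problems since the previous one (4.4.1.2), and allogeneic transfusions are logged at the in-hospital assessments (3.1, Table 1). Events can thus be placed within a visit interval:
   - 3 h (±1) to 24 h (±6): nominally 24 − 3 = 21 h, from 18 − 4 = 14 h to 30 − 2 = 28 h.
   - Consecutive daily visits, each ±6 h: nominally 24 h, from 24 − 12 = 12 h to 24 + 12 = 36 h.
   - Discharge to month 2: Table 1 gives 5 to 12 weeks after discharge, that is 35 to 84 days.

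   An event and a transfusion in the same in-hospital interval cannot be ordered from the required fields. After discharge, an event is dated only to within weeks. It is known to follow any in-hospital transfusion, but the delay is unknown, and order is lost for any transfusion given in that interval.

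5. **What the planned analyses need.** Section 6.2 tests AE proportions between groups by Fisher's exact test. That needs occurrence, which both arms supply. Section 6.3 adds analyses by transfusion type. These can be tabulated too, but without an evenly recorded onset they cannot show whether a non-serious event preceded or followed a transfusion given in the same interval.

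**The case against.** The strongest reply is that the planned safety comparison survives. All AEs and their SAE status are logged in both arms, the Fisher test needs no more than that, and the protocol plans no analysis of AE onset, duration or resolution. This stands. A reader might infer that AE rates themselves are biased by the rule, or that rates are to be compared on device-related events only. The protocol supports neither.

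A second reply is that the outcomes of most interest are captured elsewhere. This also largely stands. Creatinine and GFR or creatinine clearance are measured in every patient at screening, 3 h and days 1, 2 and 4. Wound infection and clinical signs are assessed at every postoperative check, SIRS before surgery and at 3 h and 24 h, and CRP and leukocytes serially. Medication, including antibiotics, is recorded for everyone. It would go too far to say that the renal or infection comparison depends on AE-log onset and outcome.

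Third, section 4.4.1.2 sets a minimum, and the definitions mention treatment as well as device, so a site might record more or read relatedness more widely. The control arm's Bellovac drain might prompt the same reading. But the recording rule itself says device, and the investigational product is Sangvia. Sites that read it differently would add variation between centres.

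Finally, a reader might infer that the loss is beyond repair. Monitors have access to original records (7.1), so some inpatient onset and outcome data may be retrievable. Retrieval is less assured for events after discharge.

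**Conclusion.** The point holds for non-serious AEs. The protocol ties mandatory onset, action taken and outcome to a causality category that controls cannot enter under the plain reading of the rule, while doubtful test-arm events must enter it. An even comparison of timing, action and outcome of non-serious events is lost. So is their order relative to an allogeneic transfusion within a visit interval, with timing poorest between discharge and month 2. This weakens one stated secondary objective. It does not touch the primary endpoint, AE counts or the planned AE test.

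The short-record rule applies to non-serious AEs across the planned control arm, 150 of 300 patients. That is the arm's size, not a count of affected events: the protocol gives no AE rate or share judged related, so the number of events cannot be estimated.

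The conclusion assumes that device means Sangvia, as section 3.4.1 states, and that the CRF, which is not shown, asks for no more than section 4.4.1.2 requires. A statistical analysis plan could not remedy the gap, because it cannot analyse fields that were not collected.

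**What to change.** Amend section 4.4.1.2 so that time of onset, action taken, outcome and SAE status are required, with the short description, for every AE in both arms whatever the causality call. Alongside relation to the device, record relation to any transfusion, autologous or allogeneic, so that the causality question can apply to control patients as well. No change to the planned Fisher comparison is needed.

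The cost is a few CRF fields, some extra site time per event, and handling the change as a protocol amendment under section 7.4.
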